## 8.2 Blinding

The blinding codes will be given to the pharmacist to keep and cannot be broken unless in emergency situations during the study. The treatment arrangements will be made by the pharmacist in each site, be blinded to the participants' characteristics and be not involved in the number generation and recruitment process.

## 9. DRUG ADMINISTRATION

### 9.1 Packaging and Formulation

All the participants will be received daily calcium carbonate 300 mg as the basic treatment. The participants will be orally given BSYJF capsules or placebo capsules (3 capsules per time, 3 times per day) for 36 months. All the capsules should package in identical plastic bottles (100 capsules per bottle) and subsequently delivered to the participants every 3 month at each clinical visit. All the participants will be told to take the capsules with element calcium before meal. The quality control for screening and verification of adherence to the protocol will perform by the supervisor. BSYJF/placebo will be manufactured, packaged, and distributed by Shuguang Hospital.

### 9.2 Labeling and Storage

BSYJF/placebo will be properly labeled with the product name, investigational product herbs, appropriate cautionary statement, and appropriate storage conditions. Label information for study medication boxes will comply with GCP requirements and a tag indicating 'for trial use only' will be marked.

BSYJF/placebo should be stored in the normal temperature and protected from light. Exposure to higher temperatures and vigorous shaking can lead to a loss of activity and should be avoided. The storage conditions for BSYJF/placebo must be maintained during the period of the study.

### 9.3 Administration

Detailed records of the case must be administered (date, time, and dose dispensing signature) and unused study medication to inventory count. If a subject misses a scheduled dose of capsules, the dose should be taken as

soon as possible as long as it is before the next scheduled dose, and should be resumed at the same dose. Double or extra doses should not be taken.

## 10. QUALITY CONTROL OF TEST CAPSULES

### 10.1 BSYJF Capsules

The whole BSYJF capsules processes should be produced in compliance with standards of GMP and Chinese Pharmacopoeia. Firstly, all herbal medicines will be tested in accordance with the Chinese pharmacopoeia before the production. Then, these 7 herbs will be mixed in above proportion, extracted in water, crushed into powder, and then packed into capsules (0.55g/capsule). Finally, the BSYJF capsules will be examined for the contamination with heavy metals, toxic elements, microbes and pesticide residues. The main active component in BSYJF, icariin ( $C_{33}H_{40}O_{15}$ ), should be validated and quantified by HPLC after production to confirm its pharmaceutical stability in different batches.

### 10.2 Placebo Capsules

Placebo requires no active components, which will not be used for reproducing the real efficacy of BSYJF. Therefore, mimicking the original color and taste of the BSYJF without adding any active components is a difficult procedure. The main ingredients in placebo capsules are starch supplemented with food colorants and flavoring agents to mimic BSYJF capsules. Placebo capsules are asked identical to BSYJF capsules in size, appearance, color, favor and weight.

## 11. CALCULATION OF SAMPLE SIZE (This section has been amended. Please refer to the information in “Amendment” section.)

The estimated measurement variability in BMD, muscle (lean mass of left thigh) and functional mobility is 0.72, 0.89 and 0.89, respectively. The minimum expected difference in BMD between BSYJF and placebo is defined to be 0.5. Therefore, a minimum sample size of 37 for BMD, and 55 for lean mass of left thigh and functional mobility, respectively. Each group will provide 90% statistical power at the significance level of 5% in the one-sided test.

For falls, we hypothesize that BSYJF group will lead to an annual 50% reduction, and the incidence of falls among community-dwelling elderly women is considered to 19% in the placebo group according to the previous study (Aoyagi and Ross et al., 1998; Kannus, 1999). A sample size of 110 (55 per

group) is based on a one-sided significance level of 5%, and a power of 90%. Assuming the drop-out rate is 20%, 70 patients per group will be recruited for the trial.

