### 3. BACKGROUND AND RATIONALE

#### 3.1 Hip fractures

Hip fractures cause disability and even mortality in community-dwelling elderly women, which is a devastating consequence of osteoporosis (Cooper and Barker, 1995; Zuckerman, 1996). Although many factors contribute to such fractures, the most important causes are a reduction in bone mass and an increased frequency of falls (Chapuy and Arlot et al., 1992). It is estimated that approximately 90% hip fractures in late postmenopausal women resulted from a fall (Zuckerman, 1996). It has been known that the deteriorated muscle and impaired functional mobility increases the falling risk factors obviously (Greenspan and Myers et al., 1994). Thus, it indicates that the bone-dependent risk factors including decreased bone mass and deteriorated bone micro-architecture are not the only determinant of hip fracture. In other words, the bone-independent risk factors including decreased muscle and functional mobility also play an important role in hip fracture risk factors in late postmenopausal women.

The conventional medications for preventing hip fractures only focus on bone-dependent risk factors by either inhibiting bone resorption (bisphosphonates) or promoting bone formation (rhPTH). Despite that supplement of vitamin D has demonstrated beneficial effects on muscle, there is still lack of high quality evidence to support that vitamin D alone could prevent hip fractures effectively, especially for the late postmenopausal women with osteopenia (Chapuy and Arlot et al., 1992). Therefore, it is desirable to develop alternative medications that can exert beneficial effects on reducing both bone-dependent and bone-independent risk factors.

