### 6.2 Exclusion Criteria

The postmenopausal women will be excluded from this study if:

- (1) Who had been diagnosed as having a neurological or musculoskeletal disorder, or coexisting chronic diseases;
- (2) Who have taken estrogen and calcitonin, fluoride, bisphosphonates, or adrenocortical hormone within one year;
- (3) Who had been took  $\geq 4$  prescription medications;
- (4) has environmental hazards for falls or tripping;
- (5) has impairment in gait;
- (6) has postural hypotension: drop in systolic blood pressure  $\geq 20$ mmHg or to  $< 90$ mmHg on standing;
- (7) has impairment in transfer skills or balance;
- (8) has impairment in leg or arm muscle strength or range of motion (hip, ankle, knee, shoulder, hand, or elbow) ;
- (9) has ALT or AST levels greater than 50% of upper normal limit; serum creatinine levels greater than  $133\mu\text{mol/l}$  or  $1.5\text{ mg/dl}$ .

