### 7.4 Screening and Baseline Assessment

After ICF has been obtained at the first pre-randomization visit, the consented participant will undergo initial screening which will include basic medical and

medication history, and hip BMD measurement.

At the end of the first pre-randomization visit, the consented participant will be scheduled for a second visit within about 1 week for screening. The participant will be asked to do transvaginal ultrasound and blood test to check endometrial thickness, and kidney and liver function, etc. A venous blood sample (approx. 10 ml) will be taken for blood biochemistries and a urine sample to determine if the individual meets eligibility criteria. A screening log will be recorded by each site to each candidate.

The assessment will be included:

- Medical and medication history(including history of falls);
- Physical examination (including height and weight);
- 12-lead ECG;
- Vital signs: blood pressure, temperature, pulse and heart rate;
- DXA scan of proximal femur;
- Samples: blood count, liver and kidney function, 25 (OH) vitamin D, osteocalcin, 17 $\beta$ -estradiol and urine deoxypyridinoline;
- Safety.

At the third visit, those participants who meet the eligibility criteria will be enrolled in the trial and continue with a further baseline assessment and randomization.

All participants who enter into the screening period will receive a unique subject identification number. Participants numbers will be assigned in sequential order. The subject identification number must remain constant throughout the clinical trial, that's to say, it must not be changed at the time of re-screening, enrollment, or randomization. This number will not be the same as the randomization number assigned for the study. All the participants must be subjected to physical examination, efficacy and safety assessment during the recruitment.

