#### With:

A fall is defined as any event that led to an unplanned, unexpected contact with a supporting surface. Falls resulting from pathologic fracture, major trauma or facial trauma, and/or unavoidable hazards such as transient ischemic attacks, chair collapsing or cerebrovascular accidents will be excluded. A faller is defined as the participants sustained at least one fall or more. Information about new falls while on study will be documented using form, included the date of fall and related-injury. The number of falls is accumulated. **The cumulative incidence of fallers will be calculated as the total number of participants with first fall at each time point divided by the number of participants at risk.** A copy of radiograph confirming the fracture will be obtained.

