| Eligibility criteria | 
Inclusion:
 
 
1. Women with at least 10 years after natural menopause, and aged from 55 to 69 years;
 
2. Osteopenia at least 12 months (T-score between -2.5 and -2 SD at femoral neck).
 
 
Exclusion:
 
 
1. Who had been diagnosed as having a neurological or musculoskeletal disorder, or coexisting chronic diseases;
 
2. Who have taken estrogen and calcitonin, fluoride, bisphosphonates, or adrenocortical hormone within one year;
 
3. Who had been took <math>\geq 4</math> prescription medications;
 
4. has environmental hazards for falls or tripping;
 
5. has impairment in gait;
 
6. has postural hypotension: drop in systolic blood pressure <math>\geq 20</math>mmHg or to <math>< 90</math>mmHg on standing;
 
7. has impairment in transfer skills or balance;
 
8. has impairment in leg or arm muscle strength or range of motion (hip, ankle, knee, shoulder, hand, elbow) ;
 
9. has ALT or AST levels greater than 50% of upper normal limit; serum creatinine levels greater than 133<math>\mu</math>mol/l or
 
 |

|                                   |                                                                                                                                                                                                                                                                                                                                                                                                                                                                                                                                                                                                                                                                                                                                                                                                                                                                                                                                                                            |

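### The 19% placebo fall rate behind the sample size is not justified for the lower-risk women the trial enrols, and any lower rate reduces the power for the only primary endpoint

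*Supplement*

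**What the plan says.** Section 11 (Calculation of sample size) gives the control rate for falls: "the incidence of falls among community-dwelling elderly women is considered to 19% in the placebo group according to the previous study". For the effect it says "we hypothesize that BSYJF group will lead to an annual 50% reduction". The size of 110 (55 per group) "is based on a one-sided significance level of 5%, and a power of 90" per cent, and allowing for 20% dropout gives 70 per group. Amendment 1 deletes only the paragraph of Section 11 on BMD, muscle and mobility. The falls paragraph stays in force, and the same amendment makes falls the only primary endpoint. Amendment 2 does not touch Section 11.

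The women to be enrolled are described elsewhere:

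- Section 6.1 limits age to 55 to 69, at least 10 years after natural menopause.
- Section 6.2, repeated in the Amendment 2 synopsis, excludes neurological, musculoskeletal or coexisting chronic disease, four or more prescription drugs, impaired gait, postural hypotension, and impaired limb strength or range of motion. It also excludes a woman who "has impairment in transfer skills or balance" or "has environmental hazards for falls or tripping".
- Section 3.1 says that "the deteriorated muscle and impaired functional mobility increases the falling risk factors obviously".

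No section adjusts the 19% for this selection, argues that it applies to these women, or plans a check of it. The current Section 16.3 (Amendment 1) sets all tests two-sided at 5%.

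**The concern.** The rate and the placebo arm describe different groups. The 19% is attributed to elderly women living in the community, with no further description. The trial takes a younger band and removes women for reasons that are largely fall-risk screens; one criterion names falls outright. For muscle and mobility, the protocol itself states the link to falling, then excludes impaired women and keeps the general rate.

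For a fixed relative reduction, a lower control rate means fewer fallers in both arms and less power. Falls are the only primary endpoint and the 19% is the only control rate behind it. If the true rate is well below 19%, a non-significant result could be read as no effect when too few falls occurred to tell.

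**Working it through.** **Inputs from the documents.** Placebo rate 19%, 50% annual reduction, one-sided 5%, power 90%, 55 evaluable and 70 randomised per arm (Section 11). Two-sided 5% (Section 16.3 as amended). 36 months of follow-up.

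**Assumptions.** The documents give no fall rate for the selected women, so annual rates of 17%, 15%, 12% and 10% are assumed to show a range. The 19% is read as an annual risk. Women are compared as fallers against non-fallers.

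**The plan's own figure first.** The pooled two-proportion size per arm is

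n = [z_α √(2p̄(1−p̄)) + z_β √(p1(1−p1) + p2(1−p2))]² / (p1−p2)², with p̄ the mean of p1 and p2.

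- 19% v 9.5%, one-sided 5%, 90% power: 231 per arm.
- Annual risk compounded to 36 months (46.9% v 25.9%), one-sided: 89 per arm; two-sided: 109.

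Neither gives 55. That is a separate fault, but it fixes the starting point: even at 19%, 55 per arm does not have 90% power.

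**Power as the rate falls.** For an annual placebo rate r, p1 = 1−(1−r)³ and p2 = 1−(1−r/2)³. Power = Φ{[(p1−p2)√n − z_α √(2p̄(1−p̄))] / √(p1(1−p1) + p2(1−p2))}.

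Example, r = 19%, n = 55, two-sided:

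- p1 = 1−0.81³ = 0.469; p2 = 1−0.905³ = 0.259; p̄ = 0.364.
- (p1−p2)√55 = 1.556; √(2p̄(1−p̄)) = 0.680; √(p1(1−p1) + p2(1−p2)) = 0.664.
- Φ[(1.556 − 1.960 × 0.680)/0.664] = Φ(0.335) = 63%.

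| Annual placebo rate | 36-month risk, placebo v BSYJF | Expected placebo fallers of 55 | Power, 55 per arm, two-sided (one-sided) | Power, 70 per arm, two-sided |
|---|---|---|---|---|
| 19% | 46.9% v 25.9% | 25.8 | 63% (75%) | 74% |
| 17% | 42.8% v 23.4% | 23.6 | 58% (70%) | 69% |
| 15% | 38.6% v 20.9% | 21.2 | 53% (65%) | 63% |
| 12% | 31.9% v 16.9% | 17.5 | 44% (57%) | 54% |
| 10% | 27.1% v 14.3% | 14.9 | 38% (51%) | 47% |

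**What belongs to this point.** Only the loss below the 19% row. At 55 per arm that is about 5 points at 17%, 10 at 15%, 19 at 12% and 25 at 10%. At 70 per arm it is about 5, 10, 20 and 27.

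**Other reading of the 19%.** If it is the proportion analysed (19% v 9.5%), two-sided power at 55 per arm is 30% (one-sided 41%). It falls to 26% at a placebo proportion of 17% and to 17% at 10%. The levels and the decrements differ, but the direction is the same.

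**The case against.** A reader might infer that the placebo arm is certain to fall less than 19%. The documents do not support that. They describe the source population only as community-dwelling elderly women; its age range, health restrictions and fall definition are not shown. If that population was itself fit or screened, the gap shrinks or disappears. Section 3.1 supports the link only for muscle and mobility, not for medication, home hazards or postural hypotension. This stands, and it limits the claim to probably lower, by an unknown amount.

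A reader might also infer that the whole drop from 90% to 63% comes from selection. It does not: at 55 per arm that part is present with the 19% unchanged. It comes from a size that does not follow from its inputs and from sizing one-sided for a two-sided test.

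It is also tempting to add that Section 12.3 lowers the rate further, since "Falls resulting from pathologic fracture, major trauma or facial trauma, and/or unavoidable hazards" are not counted. That holds only if the source counted such falls, which is unknown, and the causes overlap with women already excluded.

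The figures rest on choices that can be contested. Section 11 gives the 19% no time unit. If it meant a 36-month proportion, an annual rate of 6.8% would reach it (1−0.81^(1/3)), so a low-risk group could still show 19%, although one-sided power at 55 per arm would then be only 41%. The Amendment 2 synopsis analyses all randomised women, which favours the 70-per-arm column. The endpoint is worded as a number of falls, whereas the calculation counts fallers. None of this reverses the direction: power fell with the rate under every reading tried.

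**Conclusion.** The concern holds in a limited form. Section 11 applies a general-population rate, without a time unit or justification, to a placebo arm restricted in age and screened for several fall-risk factors. The rate is probably below 19%, by an amount the documents do not give. The stated 90% power is therefore not supported for the women enrolled.

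Across an assumed 19% to 10% a year, two-sided power runs from 63% to 38% at 55 per arm, or from 74% to 47% if all 70 contribute. This rests on the 50% annual reduction, 36-month compounding and a comparison of fallers. Correcting the control rate alone would not restore 90%, and correcting the arithmetic and sidedness alone would leave an unsupported control rate in place.

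**What to change.** In Section 11:

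- State the time unit of the fall rate, and say why the rate is thought to apply to women who pass Section 6.2.
- Replace the single 19% and the 90% power with the expected number of fallers and the two-sided power at 36 months, for the fixed 70 per arm (55 evaluable), over a range such as 10% to 19% a year.
- Use the fall history taken at screening as a rough guide to where in that range the trial lies. Section 7.4 lists "Medical and medication history(including history of falls" with no recall period, so this works only if the period recorded allows an annual rate. The data precede randomisation and can be pooled over arms, so no blind is broken. Recalled falls may be under-counted.

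In the conclusions, limit the result to women without the excluded risk factors.

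In Section 16.3, pre-specify fall history as a baseline covariate in the planned Cox model of time to first fall, as a prognostic adjustment. It does nothing for the chi-square test and should not be presented as narrowing the hazard-ratio interval.

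The cost is protocol and analysis-plan wording and, if usable, a short tabulation of data already collected. No extra women, visits or procedures are needed. The downside is a less favourable stated power.

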## **12. Measurements** (This section has been amended. Please refer to the information in “Amendment” section.)

During the study, every effort should be made to keep subjects on the study schedule of procedures (Table 1). These measurements should be performed at baseline and 12, 24, and 36 months. The study window is ranging from -7 to 7 days.

### **12.1 BMD and Muscle Measurement**

All the densitometry operators in the two sites should train specifically to ensure the following standard procedures. Left proximal femur (femoral neck and lean mass) in anteroposterior projection will be measured by DXA (DPX-L; Lunar, Madison, WI, USA). The same DXA apparatus should be used for a specific patient over the entire period. Monitoring of DXA scanner drift should be achieved by regular scanning of a calibration phantom.

### **12.2 TUG Test**

TUG test, consisting of both walking speed and chair rise components, is designed to evaluate the functional mobility of the participants. The participants will be instructed to rise from a standard arm chair, walk 3 meters, turn around, walk back to the chair at the normal pace and sit down (Podsiadlo and Richardson, 1991). Higher scores represent a poorer degree of functional mobility (Appendix C).

**Table 1 Schedule of Assessments**

| Assessment                      | Screening | Baseline | Treatment |        |        |
|---------------------------------|-----------|----------|-----------|--------|--------|
|                                 | Wk. -2-0  | Wk.0     | Mo. 12    | Mo. 24 | Mo. 36 |
| General information             |           |          |           |        |        |
| Informed consent                | √         |          |           |        |        |
| Medical/Medication history      | √         |          |           |        |        |
| Physical exam (Height & Weight) | √         |          | √         | √      | √      |

|                                  |   |   |   |   |   |
|----------------------------------|---|---|---|---|---|
| BMD screening                    | √ |   |   |   |   |
| Observations                     |   |   |   |   |   |
| BMD and lean mass                |   | √ | √ | √ | √ |
| TUG test                         |   | √ | √ | √ | √ |
| Falls                            |   | √ | √ | √ | √ |
| Bone biomarkers                  |   | √ | √ | √ | √ |
| Hematology                       |   | √ | √ | √ | √ |
| ECG                              |   | √ | √ | √ | √ |
| B-ultrasound                     |   | √ | √ | √ | √ |
| DDIPA                            |   | √ | √ | √ | √ |
| Adverse events                   |   |   | √ | √ | √ |
| Others                           |   |   |   |   |   |
| Drug dispensing                  |   | √ | √ | √ |   |
| Drug return                      |   |   | √ | √ | √ |
| Combined disease and Medications | √ |   | √ | √ | √ |

### 12.3 Falls Recording

A fall is defined as any event that led to an unplanned, unexpected contact with a supporting surface (Podsiadlo and Richardson, 1991). Falls resulting from pathologic fracture, major trauma or facial trauma, and/or unavoidable hazards such as transient ischemic attacks, chair collapsing or cerebrovascular accidents will be excluded. A faller is defined as the participants sustained at least one fall or more. Information about new falls while on study will be documented using form, included the date of fall and related-injury. The number of falls is accumulated. A copy of radiograph confirming the fracture will be obtained.

